## Abstract

**Background:**

Cardiac diffusion tensor imaging (cDTI) is an emerging technique for microstructural characterization of the heart and has shown clinical potential in a range of cardiomyopathies. However, there is substantial variation reported for in vivo cDTI results across the literature, and sensitivity of cDTI to differences in imaging sites, scanners, acquisition protocols, and post-processing methods remains incompletely understood.

**Methods:**

SIGNET is a prospective multi-center, observational study in traveling and non-traveling healthy volunteers. The study was initiated by the executive board of the Society of Cardiovascular Magnetic Resonance (SCMR) Cardiac Diffusion Special Interest Group (SIG) as a follow-up to a previous multi-center study on phantom validation of cardiac DTI and a recently published SCMR consensus statement on cardiac diffusion MRI. The study has been developed by the Project Management Committee in consultation with the SCMR cardiac diffusion SIG, which includes international experts in cardiac diffusion MRI. To date, more than 20 international institutions have engaged with the study, including sites that are new to cardiac DTI, making this the largest collaborative effort in the field.

**Discussion:**

SIGNET will provide important information about the key sources of variation in cardiac DTI. This will help rationalize strategies for addressing and minimizing such variation. Harmonization of protocols in this and future studies will underpin efforts to translate cardiac DTI for clinical application.

## Background

1

Cardiac diffusion tensor imaging (cDTI) is an emerging technique for microstructural characterization of the heart. The cardiac function and cardiac cellular micro-organization [1] are highly interconnected. The adult heart comprises more than a billion cardiomyocytes that change orientation in a helicoidal manner from endocardium to epicardium and contract in a highly coordinated manner to generate the cardiac output. Perturbations to the underlying microstructure are an important feature in heart muscle conditions in general. For example, an increase in collagen and scar following remodeling in myocardial infarction, or sheetlet rearrangement in hypertrophic cardiomyopathy and dilated cardiomyopathy.

The microscopic displacement of water molecules due to diffusion [2] is constrained by the presence of cells and by the properties of these cells, such as size, shape, orientation, membrane permeability, and so forth. Thus, by encoding the water diffusion information in the MR image, one can interrogate cardiac microstructure. In cDTI [3], [4], [5], for example, several diffusion encoding directions are sampled and the resulting signal is fitted using a diffusion tensor. From these diffusion tensors [6], several quantitative values can be derived such as the mean diffusivity (MD) that describes the average apparent diffusion, the fractional anisotropy (FA) that describes the eccentricity of the diffusion tensor, the principal directions of diffusivity that represent the voxel-averaged long-axis orientation of the cardiomyocytes (primary eigenvector) and the sheetlet orientation (secondary/tertiary eigenvector). Other metrics can be extracted from the diffusion tensor, such as the helix angle (HA) and sheetlet angle (E2A) that represent the voxel-averaged orientations of cardiomyocytes and sheetlets, respectively, with respect to specific reference planes.

The links between the diffusion tensor and cardiac microstructure have been validated in numerous preclinical studies [7], [8], [9], [10]. Early clinical studies have reported initial diffusion parameters in the pathologic heart. In particular, higher myocardial MD and/or lower FA have been reported in pathologies such as myocardial infarction [11], [12], [13], [14], hypertrophic cardiomyopathy [8], [15], [16], [17], [18], [19], [20], [21], [22], dilated cardiomyopathy [8], [23], aortic stenosis [24], and amyloidosis [25]. Similarly, differences in HA and E2A angles have been reported in these same conditions [8], [13], [23], [24], [25], [26]. This is thought to be related to the underlying changes in the cardiac microstructure.

The field of cDTI remains technically challenging due to factors such as cardiac and respiratory motion, image distortion, and long scan times [27], [28]. Nonetheless, the field has been rapidly expanding over the past years, with publications in cDTI more than doubling over the decade up to 2020 (PubMed search), and whole heart cDTI within clinically feasible scan times looks increasingly likely to be achievable within the foreseeable future. The main challenge thus remains the variability in measurements between vendors, sequences, and post-processing methods.

There exists a wide range of reported cDTI metrics in the literature [29], including reports that are potentially artefactual, which have been previously highlighted [30]. Other potential sources of variation include differences in sites/operators/scanners, acquisition, and post-processing methods. This variation needs to be better understood in terms of precision, accuracy, and intrinsic systematic differences in sensitivity to support clinical validation of the technique and enable clear discrimination of disease-related changes. In a first step, the Society of Cardiovascular Magnetic Resonance (SCMR) Cardiac Diffusion SIG has released a consensus statement [31] to propose a unified approach to acquire, evaluate, and report cDTI findings as basis for further studies.

Earlier work has evaluated reproducibility in a ten-site study in isotropic phantoms [32], and in a two-site study in healthy volunteers [33]. With the present study design proposal, a multi-center collaborative effort is initiated to evaluate cDTI variation due to differences in (i) site/operator/scanner, (ii) subject, (iii) acquisition strategies, and (iv) post-processing methods. The results will guide the interpretation of the cardiac diffusion magnetic resonance imaging (MRI) literature and help to refine strategies for standardization and harmonization of protocols. We propose to study healthy adult volunteers to establish a baseline of variation due to technical (non-pathology-related) factors.

1.1. Objectives

Objectives1.To evaluate variation in cDTI data due to differences in (i) site/operator/scanner, (ii) subject, (iii) acquisition strategies, and (iv) post-processing methods.2.To identify the greatest source(s) of variation, and to inform strategies for optimization, standardization, and harmonization of cDTI.3.To inform power calculations and data interpretation in future larger studies, in particular, where different sites/methods are used.

1.2. Planned outcomes

1.Optimized cDTI acquisition and post-processing methods, refined in collaboration with international expert sites.2.High-quality cDTI datasets from multiple international sites that will serve as a resource for understanding the variation in cDTI and achieving the scientific aims of the study.3.Dissemination of cDTI datasets within the study and catalyzation of developments in the field of cDTI.4.Dissemination of cDTI acquisition and post-processing methods for harmonization of methods to improve prospects of clinical translation.5.Engagement and community building in the field, and provision of support for sites who are newer to cDTI.6.Identification of new collaborations amongst and outside of the participating sites.

## Methods

2

### Study design

2.1

SIGNET is a prospective multi-center, observational study in traveling and non-traveling healthy volunteers. The study was initiated by the executive board of the SCMR Cardiac Diffusion SIG as a follow-up study to previous work on phantom validation of cardiac DTI [32] and the consensus statement on cardiac diffusion MRI [31]. The study has been developed in consultation with the SCMR Cardiac Diffusion SIG, which brings together experts from a wide range of international organizations.

Sites will participate as either (i) traveling or (ii) non-traveling volunteer sites, not both. cDTI data will be acquired using harmonized MRI sequences and repeated within the same scan session. Data will be anonymized/pseudonymized and sent to the University of Leeds (UoL) for quality control, blinding, and additional anonymisation where necessary. Anonymised data will thereafter be shared by UoL with post-processing sites for central data analysis to ensure consistency in data analysis. Data analysis will include reconstruction of cDTI parameter maps, and assessment of variation in image quality and precision of cDTI parameter maps across sites, repeats, sequences, and subjects. Identical phantoms for each site will be used for data quality checks.

### Ethics

2.2

The study has been approved by the UoL School of Medicine Research Ethics Committee (MREC 23–027) and the Health Research Authority, UK (IRAS 343837). SIGNET is registered on the 'International Standard Randomised Controlled Trial’ registry: ISRCTN46174869; registration date 12 May 2025; doi:10.1186/ISRCTN46174869. The ethics covers the recruitment and scanning of healthy volunteers by traveling volunteer sites, as well as data sharing and management across traveling and non-traveling volunteer sites. Non-traveling volunteer sites will require their own site-specific ethics that approves recruitment and scanning of healthy volunteers, as well as data sharing for future research. The approved Site Participation Checklist and Declaration has been made available to sites to guide on appropriate wording required for any new ethics or amendments required.

### Funding

2.3

Participating sites shall be fully self-funded, and cover their own costs associated with the proposed study e.g. scan fees, local data storage, administration, staff costs, phantom. Non-traveling volunteers will be reimbursed by respective recruiting sites for any costs and reimbursement. For traveling volunteers, UoL will be responsible for reimbursement of travel and expenses for traveling volunteers on behalf of traveling volunteer sites. Each traveling volunteer site will reimburse UoL for an equal share of these costs.

### Study population

2.4

Participants must satisfy the following inclusion criteria:•Healthy volunteer.•Sites shall aim to recruit equal numbers of male (N = 6) and female (N = 6) subjects.•Age 18 to 65 years old.•BMI 18.5 to 29.9.•For traveling volunteer study: Ability to travel independently between sites, and to have all scans done within 2 months from the first scan; possession of valid travel documentation.

Participants may not enter the study if any of the following exclusion criteria are known to apply:•Safety or clinical concerns precluding participation.•Any history of health conditions that may affect the heart (e.g., hypertension, diabetes, arrhythmias, angina, myocardial, valve and vessel disease, atrial fibrillation, ventricular ectopics).•Athletes (self-declared).•Any ongoing cardiovascular medication or other medication that may have secondary effects on the cardiovascular system.•Pregnancy or breast-feeding, including suspected pregnancy.•Claustrophobia which limits/prevents participants from remaining in the MRI scanner.•Inability to lie flat on the scanner table.•Physical frailty.•Contraindications to MRI (some pacemakers, intraorbital debris, intraauricular implants, intracranial clips, etc.).•Those who could be considered to have a particularly dependent relationship with an investigator, e.g. members of staff or students.•Involvement with the research apart from volunteering.•Any relevant health conditions precluding safe travel between sites within 2 months of the first scan (for traveling volunteer study).

### Sample size

2.5

A sample size of N = 12 traveling volunteers enables estimation of limits of agreement in a Bland-Altman plot to within +/−1 standard deviation of the differences between measurements. Based on previous work [33], this would be around +/−10% of the mean for both MD and FA, and applies to the comparison of any two sites, or two scans on the same subject. Inclusion of additional sites and/or subjects would improve precision of the estimate over and above this level, however, the sample size will be limited due to practical reasons. Based on the above, a sample size of N = 12 volunteers was deemed appropriate for both traveling and non-traveling volunteer cohorts, with up to an additional N = 4 as contingency in situations described below.

In exceptional cases, volunteers and/or their data may need to be excluded from the study, and replacement data acquired from other volunteer(s). For consistency, the following describes acceptable reasons for excluding volunteers and/or their data:•Scan not started or prematurely terminated e.g., due to volunteer wishes, scanner fault, etc.•Scan protocol not followed e.g., wrong sequence parameters, inclusion/exclusion criteria incorrectly applied.•Data missing or not acquired.•Data corrupted or unusable.•Incidental findings precluding participation.•Poor electrocardiogram (ECG) signal e.g., evidence of arrhythmia, high prevalence of ectopic beats or missed triggers, etc.•Poor breath-hold performance where applicable.

In the event of any of the above, sites are advised to try to rectify and repeat the failed acquisitions (within the same scan session) if possible, provided the subject is comfortable to do so. To avoid bias in data, sites are asked not to exclude volunteers or data on the basis of image quality, provided the protocol was followed correctly. Sites are to record and report reasons for exclusion of any volunteers and/or data.

The variation in cardiac DTI due to site/scanner/subject/sequence/post-processing is poorly understood, and therefore, a formal power calculation is not possible. The outputs of this study will inform such power calculations in the future.

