### Data acquisition—in vivo

2.8

Any participant undertaking an MRI scan will also complete the standard MRI safety screening on site, before any scan is undertaken.

Prospective sites will be asked to identify 1–2 sequences they wish to use for the study, and to identify which scanners they wish to use, and which software versions apply. Sequence providers, including Cleveland Clinic, CREATIS-Lyon, ETH Zurich, and RBH, will work with sites to disseminate the relevant sequences and provide a standard operating procedure (SOP) for the installation and operation of each sequence. Four sequences will be made available on two vendor platforms as shown in Table 1. Spin echo sequences will use symmetric bipolar diffusion encoding gradients with up to second order motion-compensation [3]. Options for full FOV, reduced FOV, and slice tracking [35] are provided. Stimulated echo acquisition mode (STEAM) sequences will use non-motion-compensated pulsed gradient spin echo (PGSE) monopolar gradients (Stejskal and Tanner, 1965). Sequences have been harmonized to facilitate inter-sequence comparisons. However, some variation exists e.g., use of minimum TE is specified to maximize site-specific gradient performance. A custom diffusion direction scheme is specified comprising three orthogonal directions for the b = 50 s/mm^2^ acquisition and 12 directions [36] distributed over a hemisphere for the b = 400 s/mm^2^ acquisition, with eight repetitions of each direction.

**Table 1 tbl0005:** Harmonized scan parameters for four cDTI sequences on two available vendors: (left to right) Up to M2 motion compensated spin echo (M2SE) with full FOV, M2SE with reduced FOV, M2SE with full FOV and slice tracking, and stimulated echo acquisition mode (STEAM).

			M2SE full FOV		M2SE reduced FOV		M2SE full FOV (Slice Tracking)		STEAM	
			Siemens	Philips	Siemens	Philips	Siemens	Philips	Siemens	Philips
General	Repetition time (TR)	#RR	3	3	3	3	3	3	2	2
	Echo time (TE)	ms	Select minimum. Range: 54 to 107 ms						Range: 22 to 34 ms	
	#satbands		2	2	2	OVS	2	2	0	0
	Fatsat		SPAIR	SPIR	SPAIR	SPIR	SPAIR	SPIR	CHESS	SPIR
	Bandwidth	ms	Select minimum. Range: 1900 to 2500 Hz/px							
	time@60bpm	s	360	360	360	360	360	360	360	240
	Breath-hold		N	N	N	N	N	N	Y	Y
	ECG trigger		Y							
	Trigger time (TT)	ms	= 0.85 * end-systole (max contraction) measured from cine; TT = RR to kzero							

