### Data analysis

2.11

For consistency in post-processing, cDTI data will be processed and analyzed centrally, with data processing sites blinded to the site and subject information. cDTI data from each scan will undergo the following semi-automated steps: image registration, outlier rejection, weighted or non-linear least squares fitting of diffusion tensor, generation of cDTI maps (MD, FA, HA, E2A; Fig. 4), segmentation into American Heart Association segments, reporting of parameters (e.g., mean, standard deviation, median, interquartile range) at the segment, slice and global levels. For STEAM data, actual b-values will be calculated based on recorded RR-intervals extracted from the image header information and used for fitting diffusion tensors. Signal-to-noise ratio will be assessed based on the voxel-wise standard deviation across repetitions of the same encoding [38]. Repeatability of cDTI results will be assessed by Bland-Altman plots. Data from sites will be grouped according to field strength, pulse sequence, gradient performance, and other relevant parameters, and appropriate statistical techniques will be used to examine group differences.

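### Exclusion and replacement for poor breath-holding falls mainly on STEAM, and nothing requires the excluded scans to be kept, so precision may look better than it is

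*Protocol article*

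**What the plan says.** Section 2.5 (Sample size) states that "a sample size of N = 12 volunteers was deemed appropriate for both traveling and non-traveling volunteer cohorts". A reserve of up to four more volunteers is allowed where exclusions occur. The section then lists acceptable reasons for excluding volunteers, their data, or both, with replacement data taken from other volunteers. Three of the reasons matter here: "Poor breath-hold performance where applicable", "Data corrupted or unusable", and a poor ECG signal, which includes missed triggers. The article gives no threshold for any of them.

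The same section contains safeguards:
- Exclusion is for exceptional cases.
- Sites should first try to correct the problem and repeat the acquisition in the same session.
- To avoid bias, "sites are asked not to exclude volunteers or data on the basis of image quality", on condition that the protocol was followed.
- Reasons for exclusion must be recorded and reported.

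Table 1 (Section 2.8) gives the breath-hold setting for the three M2SE variants and STEAM, each on two vendors: "Breath-hold N N N N N N Y Y". STEAM alone is breath-held. Section 2.11 adds that "Repeatability of cDTI results will be assessed by Bland-Altman plots", and Section 2.1 plans to compare precision across sites, repeats, sequences and subjects.

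**The concern.** The study exists to measure technical variation. Failure to hold a breath is part of how STEAM performs in practice, and missed triggers are plausibly part of the site, operator and scanner variation in Objective 1. Both are listed as grounds for removal before that variation is measured.

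The breath-hold reason has no counterpart for the free-breathing M2SE variants. An M2SE scan degraded by breathing but still usable falls under the rule against excluding on image quality, and stays. A STEAM scan with poor breath-holds may be removed and replaced. The scanning site decides; the blinding in Section 2.11 covers the processing sites only.

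At stake are the comparison of precision between sequences and Objective 3, since future power calculations would start from an SD that may have been trimmed.

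**Working it through.** **1. The plan's own figure.** Section 2.5 says that 12 volunteers "enables estimation of limits of agreement in a Bland-Altman plot to within" ±1 SD of the differences. The confidence level is not stated; I assume 95%, two-sided.
- Usual approximation: 1.96 × √(3/12) = 0.98 SD.
- Fuller variance: 1.96 × √(1/12 + 1.96²/(2 × 11)) = 1.00 SD.
- With t on 11 degrees of freedom in place of 1.96: 1.10 and 1.12 SD.

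The figure reproduces. It is expressed in units of the SD, so replacing volunteers to hold N at 12 leaves it unchanged. What selective removal changes is the SD itself.

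**2. Which data each reason can reach.**

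| Reason in Section 2.5 | M2SE diffusion data | STEAM diffusion data |
|---|---|---|
| Poor breath-hold | not breath-held (Table 1) | yes |
| Poor ECG, missed triggers | yes | yes |
| Corrupted or unusable | yes | yes |
| Degraded by breathing but usable | must be kept | may leave under the breath-hold reason |

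**3. Effect on the SD.** Inputs, both assumed because the documents give neither: a share p of STEAM repeat pairs comes from poor breath-holding, and the SD of their differences is r times the usual one. With equal means, the SD over all pairs is √(1 − p + p·r²) times the SD over the retained pairs. The width of the limits of agreement is proportional to the SD, so the understatement is 1 − 1/√(1 − p + p·r²).

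| p | r | 1 − p + p·r² | Square root | Understatement |
|---|---|---|---|---|
| 5% | 2 | 1.15 | 1.072 | 6.7% |
| 10% | 2 | 1.30 | 1.140 | 12.3% |
| 10% | 3 | 1.80 | 1.342 | 25.5% |
| 20% | 3 | 2.60 | 1.612 | 38.0% |

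A wider grid (p from 10% to 30%, r from 1.5 to 3) gives about 6% to 46%. With p = 0 the understatement is zero.

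**4. What the limit of four allows.** Four extra volunteers on 12 means that up to 4 of 16 scanned (25%) can be replaced. The chance of needing more than four replacements before reaching 12 acceptable volunteers is 1 − Σ C(11+k, k)·p^k·(1−p)^12 over k = 0 to 4. This is 1.7% at p = 10%, 20% at p = 20% and 55% at p = 30%. The limit hardly restrains the 10% cases but makes the largest ones less likely.

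**5. A bounding case for normal differences.** Simulation (100,000 runs) removed the k largest absolute differences from 12 + k. The remaining SD was 0.86, 0.77, 0.70 and 0.64 of the true value for k = 1 to 4, so 36% too small at most. The 38% in step 3 can exceed this because that mixture has heavier tails than a normal distribution.

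**6. Consequence for planning.** Where the repeat SD is the planning variance, the required sample size scales with SD². At p = 10%, r = 2 a later study would be planned with 1/1.30 = 77% of the volunteers it needs.

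**The case against.** A reader might infer that the rule removes STEAM's failures only, that M2SE keeps all its poor data, and that the comparison is therefore biased. The documents do not support that reading:
- The ECG, usability, missing-data and early-termination reasons apply to every sequence.
- Every session starts with breath-hold cine views, from which the trigger time is set (Section 2.8), so poor breath-holding can also affect an M2SE session.
- If a whole volunteer is dropped at a site running both sequences, that volunteer's M2SE data go too.

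Nor is there an outright contradiction with the rule on image quality. That rule holds only if the protocol was followed, and breath-holding is part of the STEAM protocol. Precision given a correctly executed scan is also a legitimate quantity to estimate. Parameter maps are made centrally under blinding, and nothing suggests that sites select on MD, FA or repeat differences. Thresholds may stand in the operating procedures, which are not shown, so their absence from the article is not the finding.

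All of this stands, and it reduces the point to a risk. It does not remove it. The article lets a site drop the data without the volunteer, and sites choose one or two sequences, so STEAM and M2SE cohorts can be filtered differently. Reported reasons give counts, not the lost measurements. A repeat in the session can take the place of a failed first attempt without any stated duty to keep the first.

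**Conclusion.** The point holds as a risk of optimistic precision, greatest for STEAM. A site-judged exclusion reason that bears mainly on one sequence is coupled to replacement in a study that compares sequences, and the stated safeguards do not preserve what is removed.

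The size cannot be obtained from the documents. Limits of agreement would be about 7% to 38% too narrow under the assumed shares and SD ratios. The upper end needs one STEAM pair in five removed with a tripled SD, which sits poorly with exceptional use and repeats in session. The effect is zero if the reason is never used. The analysis cannot repair this later if the scans were not kept, so the matter belongs in the protocol.

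**What to change.** Amend Section 2.5 as follows:
- Every acquired dataset, including failed first attempts repeated in the session, is uploaded and kept, with a flag for breath-hold, trigger or usability problems.
- Repeatability and precision between sequences are reported both with and without flagged scans that can still be processed.
- Failure and replacement rates are reported by sequence and site.

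Exclusions for wrong parameters, ineligibility, scans not started and incidental findings may stand. If an operating procedure already requires full upload, Section 2.5 need only say so and add the reporting.

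The cost is one protocol paragraph, an upload instruction, some extra storage and processing, and a second run of the precision analysis. Limits of agreement in the all-data analysis will be somewhat wider. The change should be made before further scanning, because discarded scans may not be recoverable.
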